**CONFIDENTIAL**

# **A Randomized, Double-Blind, Sequential Study to Evaluate the Safety, Immunogenicity, and Cellular Immunity of the Universal Recombinant COVID-19 (NVSI-06-09) Vaccine versus the Inactivated COVID-19 (Vero Cell) Vaccine in Adults Previously Immunized with the Vero Cell Vaccine**

## **1. INTRODUCTION**

The recombinant COVID-19 vaccine (NVSI-06-09) was developed by Sinopharm CNBG National Vaccine & Serum Institute (NVSI) affiliated to China National Biotec Group Co., Ltd. (CNBG) is used to prevent the diseases caused by SARS-CoV-2. NVSI, Lanzhou Institute of Biological Products Co., Ltd. (hereinafter referred to as "LIBP") and Beijing Institute of Biological Products Co., Ltd. (hereinafter referred to as "BIBP") affiliated to CNBG, jointly applied as Sponsors to carry out clinical trials on this product.

In this project, a randomized, blinded, positive control method will be used to evaluate the safety and immunogenicity of booster immunization of Recombinant COVID-19 Vaccine (NVSI-06-09) in a healthy population aged 18 years and above. This study was approved by the Ministry of Health of UAE.

## **2. BACKGROUND AND PRINCIPLE**

### **2.1 Background of disease**

According to WHO data, as of January 10, 2022, there were 305,914,601 confirmed cases and 5,486,304 deaths due to COVID-19, with a mortality rate of 1.8%. The infection sources of COVID-19 are mainly SARS-CoV-2 infected patients and asymptomatic infected persons, but it is found that patients in the incubation period are also contagious, and they are highly contagious within 5 days after onset. SARS-CoV-2 is mainly transmitted through respiratory droplets and close contact, which may be transmitted by aerosol. Contact with virus-contaminated articles can also cause infection. Because SARS-CoV-2 can be isolated from patients' faeces and urine, environmental pollution caused by faeces and urine can also cause aerosol or contact transmission. People are generally susceptible, and they can become infected at any age. People can get certain

**CONFIDENTIAL**

immunity after infection or vaccination with the COVID-19 vaccine, but the duration is not clear. Based on the current epidemiological investigation, the incubation period of the virus is generally 1 ~ 14 days, mostly 3 ~ 7 days, and the incubation period of very few cases can reach 24 days.

The main clinical symptoms of COVID-19 are fever, dry cough and fatigue, and the first symptoms of some patients are loss of smell and taste. A few patients are accompanied by nasal congestion, runny nose, sore throat, muscle pain and diarrhoea. According to clinical symptoms, it can be divided into four categories: mild, moderate, severe and critical. Severe patients often have dyspnea and/or hypoxemia one week after onset, and severe patients can rapidly progress to acute respiratory distress syndrome, septic shock, metabolic acidosis, coagulation dysfunction and multiple organ failure. Very few patients may also have central nervous system involvement and microvascular necrosis. It is worth noting that severe and critical patients may have moderate to low fever or even no obvious fever during the disease course. Mild patients may show low fever, slight fatigue, smell and taste disorders, etc., without pneumonia. A few patients have no obvious clinical symptoms after being infected with SARS-CoV-2. According to the current cases, most patients have a good prognosis, while a few patients are in critical condition. The prognosis of the elderly and those with chronic basic diseases is poor. The clinical process of pregnant women with COVID-19 is similar to that of patients of the same age. Paediatric patients have relatively mild symptoms.

## **2.2. Pathogenic background**

SARS-CoV-2 belongs to  $\beta$  coronavirus. Under a cryoelectron microscope, it is approximately spherical particles with variable diameters, mainly around 100nm. SARS-CoV-2 contains a dense virus matrix, surrounded by a lipid bilayer, and its outer surface protrudes. It is an enveloped virus, which is composed of non-segmental positive-sense single-stranded RNA and protein. It belongs to Orthocoronavirinae and is widely distributed in humans and other mammals.

The genome of the SARS-CoV-2 strain is 29.9 kb long and encodes 9860 amino acids. SARS-CoV-2 has four main structural proteins, known as spike protein (S), membrane protein (M), an envelope protein (E) and nucleocapsid protein (N), as well as several helper proteins. S, M and E proteins constitute the viral envelope and are the main surface antigens of a virus-induced immune

**CONFIDENTIAL**

response. S protein is a transmembrane glycoprotein with a molecular weight of about 150kDa, which is divided into two subunits, namely S1 and S2, by the Furin protease of host cells. S1 contains one RBD, which is responsible for determining the cell-targeting between host cells and virus receptor binding domains; As a membrane fusion subunit, S2 can mediate virus to fuse with host cells. M protein plays an important role in determining the shape of the viral envelope. It can bind with other structural proteins, and binding with N protein helps to stabilize nucleocapsid and promote the assembly of the virus. E protein plays an important role in the process of virus production and maturation. N protein is located in the core of the virus and combines with viral RNA to form nucleocapsid. N protein has a highly conserved sequence, and it participates in virus replication and infection of host cells.

The binding of spike protein (S protein) with angiotensin-converting enzyme 2 (ACE2) protein is essential for SARS-CoV-2 infecting human cells. After fusion, transmembrane protein serine 2 (TMPRSS2), which exists on the surface of host cells, scavenges ACE2 and activates S protein. Activation of the S protein causes a conformational change and allows the virus to enter the host cell. The affinity of S protein of SARS-CoV-2 with ACE2 is 10 to 20 times that of the SARS virus, which may be the reason for the strong transmission of COVID-19. ACE2 expressed in respiratory epithelial cells and type II alveolar cells of the lung is the receptor of SARS-CoV-2 entering host cells. Besides lung, ACE2 is also distributed in intestinal epithelial cells of the ileum and colon, vascular smooth muscle cells, proximal tubular epithelial cells of the kidney, urinary tract epithelial cells of the bladder and testis. Therefore, COVID-19 patients will not only have respiratory diseases, but also have heart, kidney, and digestive system diseases. ACE2 expression in vascular intima can damage endothelial cells and lead to the risk of thrombotic events. In addition, the immune system releases a large number of cytokines to viral infection sites or secondary infection, which can induce cytokine storm and septicemia symptoms.

In addition, coronavirus is sensitive to ultraviolet rays and heat. For 30 minutes at 56 °C, ether, 75% ethanol, chlorine-containing disinfectant, peracetic acid and chloroform can effectively inactivate the virus, but chlorhexidine cannot effectively inactivate the virus.

### **2.3. Vaccine background**

**CONFIDENTIAL**

As of January 2022, there are 36 COVID-19 vaccines have been approved for use in at least one country/region around the world, including 3 mRNA vaccines, 6 viral vector vaccines, 11 inactivated vaccines, 15 recombinant protein vaccines, and 1 DNA vaccine.

According to the statistics from the World Health Organization (WHO) as of January 7th, 2022, there are 331 COVID-19 candidate vaccines active in the R&D stage, among which 137 are at the clinical development stage. There are 146 recombinant protein vaccines, which accounted for 44.1% of all types of vaccines, 47 of which are at the clinical stage. A total of 7 vaccines in China have obtained conditional approval or emergency use authorization, including 5 inactivated vaccines (Sinopharm CNBG BIBP, WIBP, Sinovac, Kangtai Bio and Institute of Medical Biology, Chinese Academy of Medical Sciences), Cansino's recombinant adenovirus vector vaccine (injection type) and Zhifei biological's recombinant protein vaccine (CHO cell). Among them, two inactivated vaccines produced by CNBG-BIBP and Sinovac have been approved by WHO in 2021 and included in the emergency use listing. The recombinant protein vaccine developed by Zhifei Bio has been authorized for emergency use in China, and others are in Phase I/II study. And four inactivated vaccines, four recombinant viral vector vaccines and four nucleic acid vaccines are in Phase III clinical trial.

### **2.3.1 Inactivated Vaccine**

The inactivated vaccine is made from a virus that has been grown in cell culture and have been lose its pathogenicity by physical or chemical method but only retain its antigenicity. As a traditional vaccine preparation method, the process is mature. At present, there are 29 inactivated vaccines under research around the world, of which 18 are at the clinical stage. Five inactivated vaccines in China have been approved for conditional marketing or emergency use authorization, including Sinopharm CNBG BIBP, WIBP, Sinovac, Kangtai Bio and Institute of Medical Biology, Chinese Academy of Medical Sciences.

### **2.3.2 Recombinant Protein Vaccine**

Compared with other types of vaccines, recombinant protein vaccines are one of the key directions of research and development in novel vaccines due to the significant advantages in safety and low cost. At present, 146 COVID-19 recombinant protein vaccine candidates are under development,

**CONFIDENTIAL**

and 47 of them are at the clinical stage.

### **2.3.3 Recombinant Viral Vector Vaccine**

Viral vector vaccine uses replicative or non-replicative viruses as vectors, recombine specific antigen gene fragments into the vector genome, deliver them into host cells, and induce expression and induces a corresponding immune response. Currently, there are 97 recombinant viral vector vaccines in R&D, 27 of them are at the clinical stage, 6 vaccines have been approved for use in at least one country or region.

### **2.3. 4 Nucleic Acid Vaccine**

Nucleic acid vaccines introduce DNA or mRNA encoding specific antigens into human cells, express corresponding antigen proteins, and induce an immune response. Currently, there are 78 nucleic acid vaccines in active research and development, and 38 vaccines at the clinical stage, including 23 mRNA vaccines and 15 DNA vaccines.

## **3. STUDY OBJECTIVE**

To evaluate the safety and immunogenicity of booster vaccination of Recombinant COVID-19 Vaccine (NVSI-06-09) developed by Sinopharm CNBG National Vaccine & Serum Institute in a healthy population aged 18 years and above.

### **3.1. Primary Objectives**

1. To compare the immunogenicity (prototype SARS-CoV-2 Omicron variant stain) of NVSI-06-09 vaccine with Vero Cell vaccine, 14 days after a single dose of the booster vaccine in adults  $\geq 18$  years of age.
2. To compare the safety of NVSI-06-09 vaccine with Vero Cell vaccine, 28 days after a single dose of the booster vaccine in adults  $\geq 18$  years of age.

### **3.2. Secondary Objectives**

1. To compare the immunogenicity (prototype SARS-CoV-2 Omicron variant stain) of NVSI-06-09 vaccine with Vero Cell vaccine, 28 days after a single dose of the booster vaccine in

**CONFIDENTIAL**

adults  $\geq 18$  years of age.

2. To compare the immune persistence of booster immunization using recombinant COVID-19 vaccine (NVSI-06-09) and inactivated COVID-19 vaccine (Vero cell) in populations  $\geq 18$  years of age.
3. To compare cellular immunity after immunization with NVSI-06-09 vaccine or Vero Cell vaccine in adults  $\geq 18$  years of age.

### **2.3 Exploratory Objectives**

1. To evaluate the efficacy of NVSI-06-09 vaccine against COVID-19, especially severe cases (including deaths), 14 days after booster vaccine administration.
2. To compare the cross-protection effects of NVSI-06-09 vaccine against COVID-19 Variants of Concern (VoC) such as Alpha, Beta, Delta, and Omicron), 14 and 28 days after a single dose of NVSI-06-09 administration.

## **4. STUDY DESIGN**

### **4.1. Trial Description**

This clinical trial adopts a randomized, double-blind and positive controlled design.

### **4.2. Procedures and Methodology**

#### **Sample size:**

A total of 516 healthy participants aged 18 years and above who have been vaccinated with 2/3 doses of inactivated COVID-19 vaccine, will be enrolled, and randomly assigned to the experimental group and control group in a 1:1 ratio, with 258 participants in each booster group.

#### **Immunization Schedule:**

Among the participants who have been vaccinated with two/three doses of inactivated COVID-19 vaccine (Vero cell) for  $\geq 6$  months, one dose of recombinant COVID-19 vaccine (NVSI-06-09) (NVSI-06-09) or inactivated COVID-19 vaccine (VERO cell) will be immunized boosterly.

#### **Route of Administration:**

**CONFIDENTIAL**

Lateral deltoid muscle of the upper arm, intramuscular injection

**Safety Observation:**

The participants will be observed at the study site for 30 minutes after immunization, and local and systemic adverse events will be actively collected and recorded on the diary cards within 0-7 days. Perform one safety follow-up per week to collect AEs and record them in the follow-up system. Serious adverse events (SAEs) will be monitored within 12 months after immunization and follow-up, recorded and report according to requirements.

**Immunogenicity Observation:**

Blood samples of all the participants will be collected before the vaccination of booster dose and 14 days, 28 days, 3 months, 6 months, 9 months and 12 months after booster vaccination for detection of neutralizing antibodies. The neutralizing antibody will be tested by a micro-dose cytopathogenic effect (CPE) assay.

**Cellular Immunity Observation:**

A total of 20 participants from each study group will be sequentially invited to give 5 additional venous blood samples (12ml per participant per sample). PBMC was separated, and the activation of specific T cells were detected by ELISPOT and flow cytometry. T-cell receptor (TCR) characteristics of specific T cells and B-cell antigen receptor (BCR) characteristics of B cells are analyzed using high-throughput single-cell sequencing to analyze the type and proportion of immune cells in PBMC, as well as the expression profile of immune-related genes in each subgroup of cells. Specific time points of blood sample collection are described in Table 2 Sample Size and Procedures of Clinical Trial.

**Table 2. Sample size and Procedures of Clinical Trial**

| Previous Immunization (No. doses and timeline) | Intervention Group (Booster Vaccine) | Sample Size (N) | Safety | Immunogenicity Blood Collection Time Point | Cellular immunity Blood Collection Time Point |
|------------------------------------------------|--------------------------------------|-----------------|--------|--------------------------------------------|-----------------------------------------------|
|------------------------------------------------|--------------------------------------|-----------------|--------|--------------------------------------------|-----------------------------------------------|

CONFIDENTIAL

|                                                                                  |                       |     |                                                                                                                     |                                                                                                                                                                                                                                                                                                   |                                                                                                                                                                    |
|----------------------------------------------------------------------------------|-----------------------|-----|---------------------------------------------------------------------------------------------------------------------|---------------------------------------------------------------------------------------------------------------------------------------------------------------------------------------------------------------------------------------------------------------------------------------------------|--------------------------------------------------------------------------------------------------------------------------------------------------------------------|
| Vero Cell Vaccine
(2 or 3 doses,
≥6 months prior
to study
screening) | NVSI-06-09
Vaccine | 258 | Safety data is
collected after
booster vaccine
administration.                                             | Blood samples are
collected during the
following study
visits:                                                                                                                                                                                                                           | Blood samples are
collected during the
following study
visits:                                                                                            |
|                                                                                  | Vero Cell
Vaccine  | 258 | Solicited AEs
collected
within 30
minutes via
onsite
observation
and 0-7 days
via diary cards. | Before booster
vaccine
administration:
• Visit 1 (D0)*                                                                                                                                                                                                                            | Before booster
vaccine
administration:
• Visit 1 (D0) *                                                                                            |
| Total sample size (N)                                                            |                       | 516 | Unsolicited
AEs collected
within 8-30
days via safety
visits.                                           | After booster
vaccine
administration:
• Visit 4 (D14) a
• Visit 6 (D28) a
• Visit 8
(3M after V1) b
• Visit 11
(6M after V1) b
• Visit 12
(9M after V1) b
• Visit 13
(9M after V1) b | After booster
vaccine
administration:
• Visit 4 (D14) a
• Visit 6 (D28) a
Visit 11 (D28) (6M
after V1) b |
|                                                                                  |                       |     | SAEs collected
up to 12
months
following the
booster dose
via safety
visits.                      |                                                                                                                                                                                                                                                                                                   |                                                                                                                                                                    |

**Abbreviations: N: number, D: days, M, months.**

a Blood collection window at D14 and D28 is +10 days

b Blood collection window at 3M, 6M, 9M, 12M is +30 days.

### 4.3. Study Endpoint

**CONFIDENTIAL**

**Primary Endpoints:**

1. GMT and the 4-fold rise rate of anti-omicron neutralizing antibody 14 days after a single dose of the booster vaccine in adults  $\geq 18$  years of age.
2. The incidence and severity of any adverse reactions/events within 30 minutes after vaccination;
3. The incidence and severity of solicited adverse reactions/events within 0-7 days after vaccination;
4. The incidence and severity of unsolicited adverse reactions/events within 8-30 days after vaccination;
5. The incidence of SAE and AESI observed after vaccination and up to 12 months after full course of immunization.

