#### 4.5 Safety Observation Indicators and Grading Criteria

##### 4.5.1 Safety Observation Indicators

###### (1) Adverse events collected in 0-7 days

**Local adverse events:** pain, induration, swelling, rash, redness and pruritis.

**Systemic adverse events:** fever, diarrhoea, constipation, dysphagia, anorexia, vomiting, nausea, myalgia (systemic), arthralgia, headache, cough, dyspnoea, systemic pruritis (no skin damage), abnormal skin mucosa, acute allergic reactions, tiredness/fatigue, and dizziness

**Other adverse events:** any medical events other than the above mentioned during clinical studies, such as acute diseases, accidental injuries, etc.

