###### (2) Adverse events collected in 8-28 days

**CONFIDENTIAL**

Any medical events, such as acute diseases and accidental injuries occurred during 8~28 days in clinical studies.

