### **(3) Pregnancy events**

Collect all pregnancy events and outcomes between vaccination and the end of the study (6 months after a full course of immunization). Follow-up of the newborns should last at least 1 month after birth.

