**CONFIDENTIAL**

respectively, the participants were followed-up by telephone and guided to observe the adverse events correctly and fill in the diary card.

3. On the 14th day after vaccination, the investigator reviews the filling of the diary card during this period and re-collect the diary card.
4. On the 8th -28th day after vaccination, the investigator uses telephone follow-up once a week, combined with an active report of the participants to monitor the safety.
5. When it is known that the participant has adverse reactions/events of Grade 3 or above, a face-to-face visit should take place within 24 hours.
6. SAEs and AESIs are observed from the first dose to 12 months after the full course of vaccination via monthly telephone follow-up calls and self-reports from the participants.
7. Participants should contact the doctors on informed consent form/diary card immediately if developed any COVID-19 like symptoms.

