### **9. COMPLETION OF CLINICAL TRIAL**

After obtaining the immunogenicity test results 14 days after the full course of immunization, completing the safety follow-up for 28 days, ensuring the authenticity, integrity and accuracy of clinical trial data, the database is locked and unblinded to perform safety, immunogenicity and vaccine efficacy evaluation, and blood collections for 12 months immune persistence are completed, the study site will be closed.

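### Primary safety endpoint 4 counts unsolicited events only from day 8, so non-listed events of days 0-7 enter neither endpoint 3 nor 4; its day-30 end also conflicts with the 28-day window used elsewhere

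*Protocol*

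**What the plan says.** Section 4.3, repeated in the Synopsis, sets four primary safety endpoints:

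- Endpoint 2: "The incidence and severity of any adverse reactions/events within 30 minutes after vaccination".
- Endpoint 3: "The incidence and severity of solicited adverse reactions/events within 0-7 days after vaccination".
- Endpoint 4: "The incidence and severity of unsolicited adverse reactions/events within 8-30 days after vaccination".
- Endpoint 5: SAE and AESI from vaccination to 12 months.

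Section 4.5.1 defines what is collected. For days 0-7 it lists local terms, systemic terms and a third category: "any medical events other than the above mentioned during clinical studies, such as acute diseases, accidental injuries, etc". For the later period it collects "Any medical events, such as acute diseases and accidental injuries occurred during 8~28 days in clinical studies".

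Tables 1 and 2 state that unsolicited events are collected in days 8-30 through safety visits. Primary objective 2 compares safety at 28 days, and Section 9 makes "completing the safety follow-up for 28 days" a condition of database lock.

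For longer follow-up, Section 7.3.1 item 6 says "SAEs and AESIs are observed from the first dose to 12 months after the full course of vaccination via monthly telephone follow-up calls and self-reports". Section 4.5.1(3) collects pregnancies up to "the end of the study (6 months after a full course of immunization", whereas Section 7.10 closes sites after 12 months of safety observation and blood collection.

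**The concern.** Endpoints 3 and 4 split the follow-up by event type and by time at once: solicited before day 8, unsolicited from day 8. The split works only if nothing unsolicited is recorded before day 8, and Section 4.5.1(1) shows that such events are recorded. The collection text describes almost the same kind of event before and after day 7, yet it counts toward a primary endpoint only in the later period.

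A count of unsolicited events made strictly to endpoint 4 will therefore differ from the unsolicited count that Section 10.3.4 produces, because that section sets no day window. With two end days in the text as well, the same dataset could support more than one figure for a primary safety endpoint, and the choice could be made after unblinding.

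**Working it through.** No sample size, power or alpha figure is involved. The check sets the windows side by side and counts calendar days inclusively, with day 0 as the day of vaccination.

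**1. Where a non-listed event lands**

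| Onset of a non-listed event | Collected under | Endpoint 2 | Endpoint 3 | Endpoint 4 | Endpoint 5 |
|---|---|---|---|---|---|
| First 30 minutes | 4.5.1(1) | yes | no | no | only if SAE/AESI |
| After 30 minutes, to day 7 | 4.5.1(1) | no | no | no | only if SAE/AESI |
| Days 8-28 | 4.5.1(2) | no | no | yes | only if SAE/AESI |
| Days 29-30 | Tables 1-2 only | no | no | yes | only if SAE/AESI |

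The second row is the gap. A non-serious, non-AESI event of this kind enters no primary safety endpoint. It cannot be treated as solicited, because Section 4.5.1(1) lists the category apart from the local and systemic terms.

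**2. Size of the gap in follow-up time**

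- Days 0-7: 7 - 0 + 1 = 8 days.
- Days 0-28: 28 - 0 + 1 = 29 days, so 8/29 = 28%.
- If the end day is 30: 30 - 0 + 1 = 31 days, so 8/31 = 26%.

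**3. End of the window**

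- Day 30: endpoint 4 in Section 4.3 and the Synopsis; Tables 1 and 2.
- Day 28: primary objective 2; the Synopsis safety text; Sections 4.5.1(2), 7.3.1, 7.3.2 and 7.6; the lock condition in Section 9.
- Endpoint 4 spans 30 - 8 + 1 = 23 days and the Section 4.5.1(2) window 28 - 8 + 1 = 21 days. The disputed part is 2 of 23 days (9%).
- The schedule of events has no day-30 visit. Visit 6 is at day 28 with a window of +10 days, and Visit 7 is at 2 months.

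**4. Long-term follow-up**

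- The schedule's telephone row is ticked at V1-V3, V5 and V7-V11, and not at V12 (9 months) or V13 (12 months).
- Monthly calls after month 6 would be 12 - 6 = 6. The schedule shows no telephone tick in that period and two visits, at 9 and 12 months.
- End of study: 6 months in Section 4.5.1(3), 12 months in Section 7.10.

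**5. What the analysis section does with the events**

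Section 10.3.4 summarises all TEAEs, vaccine-related TEAEs and Grade 3 or higher TEAEs by group, compares groups with Fisher's exact test, and adds a solicited/unsolicited split. None of these has a day window, so non-listed events of days 0-7 are included.

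**The case against.** The strongest reply is that little is lost in practice. The events are collected, Section 10.3.4 compares all TEAEs between groups, endpoint 2 takes any event in the first 30 minutes, and endpoint 5 takes every SAE and AESI. Six local and 17 systemic terms are already solicited in the first week. No hypothesis or sample size rests on these windows. All of this stands, and it limits the point to the definition of the endpoint. It does not remove it: Section 10.3.4 gives no window that would correct endpoint 4, and a later analysis document should not have to override a stated primary endpoint.

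Three stronger readings are tempting and are not supported:

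- *The safety comparison leaves out early unsolicited events.* Only the primary endpoint as worded does; the planned TEAE comparison includes them.
- *Days 29-30 are not collected.* That follows from Sections 4.5.1(2) and 7.3.1, but Tables 1 and 2 say collection runs to day 30, and Visit 6 may fall after day 30. The documents show a contradiction, not an absence of data.
- *SAE and AESI capture lapses after month 6.* Section 7.3.1 still requires monthly calls and self-reports to 12 months, and Tables 1-2 collect SAEs to 12 months. The schedule's SAE row carries a single tick, probably a merged cell lost when the table was read, so it settles nothing. The telephone row omits calls that the text requires. Pregnancy capture is not part of endpoint 5, so its 6-month limit says nothing about SAE or AESI capture.

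**Conclusion.** The point holds as a defect in the wording of a primary endpoint. Non-listed events of days 0-7, 8 of the 29 calendar days 0-28 (28%), fall outside both endpoint 3 and endpoint 4, except for the parts that endpoints 2 and 5 pick up. The data are collected and enter the planned TEAE summaries. The 28-day and 30-day windows contradict each other across the protocol, as do the two long-term follow-up pairs.

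This rests on reading the third category in Section 4.5.1(1) as unsolicited, which its separate listing and its near-identical description for days 8-28 support. The 28% is a share of follow-up days. The protocol gives no event rates, so the share of events affected cannot be derived, and incidence is in any case counted per participant.

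**What to change.** - Start endpoint 4 at day 0 in Section 4.3 and the Synopsis, and change the matching collection cell in Tables 1 and 2. Some first-30-minute events would then count under endpoints 2 and 4. Solicited events already overlap in this way between endpoints 2 and 3, so no new problem arises.
- Reconcile the end day, 28 or 30, so that the endpoint, the safety objective, the collection sections (4.5.1, 7.3.1, 7.3.2, 7.6), Tables 1-2 and the Section 9 lock condition use one window. The documents do not settle which day is intended.
- Separately, reconcile the schedule's telephone row with Section 7.3.1 item 6, and the end of study in Section 4.5.1(3) with Section 7.10.

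The endpoint change costs only wording, since Section 4.5.1(1) already collects the day 0-7 events. Reconciling the telephone row costs nothing if the calls are already made as Section 7.3.1 requires, and a small number of calls if they are not. All of it should be settled before unblinding.
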